###### Leaving the study early

Perceived reasons for withdrawal will be recorded.

###### Inappropriate use of prescribed medication

Examples of this include intentional overdose and storing, trading, swapping or selling of prescribed medication.

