## Background

In the United Kingdom (U.K), there is an extensive market for the sale of heroin, an illicit class 'A' drug. Precise figures of how many people use and are dependent on heroin are difficult to establish as there has never been a national prevalence survey [1]. The link between crime and illicit drug use, specifically heroin use, is well recognised. In 2002, 63% of injecting drug users (IDUs) in contact with specialist drugs services in England and Wales reported having ever been in prison or a young offenders' institution [2]. Those addicted to illicit opiates such as heroin require medical help in reducing and stopping their use due to the drug's highly addictive properties.

Neither the current evidence base [1] nor the national guidelines on the clinical management of drug misuse [3] stipulate a 'drug of choice' for rapid opiate detoxification. In the absence of an established evidence base, a wide variety of agents have therefore been used including methadone, dihydrocodeine, buprenorphine, lofexidine and clonidine. Historically within prisons, the most commonly used drug for opiate detoxification has been dihydrocodeine. Anecdotally this was because of a reluctance to prescribe methadone following a small number of methadone related deaths in the prison setting. Dihydrocodeine is attractive to clinicians as it has a shorter half-life than methadone, and seems equally acceptable to users. However, there has been a move away from prescribing dihydrocodeine due to its potential for diversion by prisoners into the prison shadow economy. Increasingly, buprenorphine is now being prescribed and recent policy supports methadone prescribing [4]. Buprenorphine – in the form of sub-lingual tablets – is relatively new for the purpose of opiate detoxification in the UK, especially within the prison estate. It has the potential advantage of having a good safety profile, better retention in treatment and lower withdrawal severity when compared to methadone, lofexidine or clonidine [5-8]. Her Majesty's Prison (HMP) Leeds saw a 42% increase in buprenorphine prescribing between April 2002 and January 2004. Buprenorphine is increasingly being prescribed in the community [9].

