## Methods

### Design

LEEDS is a pragmatic open label randomised controlled trial.

Randomisation will be random block size, which will be administered centrally in the Academic Department of Psychiatry and Behavioural Sciences, University of Leeds. Opaque consecutively numbered envelopes will be prepared. If a prisoner is both eligible and agreeable the next envelope will be opened and the intervention allocated.

Confounding variables i.e. doctor participant relationships, drugs worker participant relationships will all be controlled for by randomisation. Some confounding variables cannot be randomised. These include the inherent difference in the two detoxification programmes, i.e. the daily supervised consumption of buprenorphine.

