#### Secondary outcomes

##### During the period of detoxification

###### Adverse events

Clinicians will record any details of adverse events in the usual way i.e. an entry will be made in the participants' records. Those adverse events clearly resulting in clinically significant distress to study participants or of major concern to clinicians will be recorded. The LEEDS trial co-ordinator will extract data from clinical records, for the period of detoxification, and transcribe these to a database.

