#### Data collection

The outside of the allocation envelope will be completed by the prison doctor before opening. This will record Unit number, date of birth and estimate of severity of addiction and expected prognosis.

The LEEDS trial co-ordinator will collect details of drug of allocation, background history, and use of opiates from the participant's health records. The primary outcome and data at one, three months and six months after randomisation will again be collected by the LEEDS trial co-ordinator. There will be minimal additional contact with the participants. LEEDS is designed to avoid the complication of the care provided to this group.

All data will be double entered into an EPI-INFO database customised for the LEEDS project and the simple analysis involved with this project will also be undertaken in that package.

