#### Analysis

After data entry, all analysis will be undertaken in Epi-info. The analysis of the primary outcomes will be of a simple 2 × 2 table (see Table 4, below). Dummy tables have been constructed for all secondary outcomes. These tables are designed to be rigid templates for the final write up of the project, and to protect the researchers from bias, once the data are disclosed. An example is given below, but dummy tables for all data to be collected have been constructed, *a priori*, for every variable to be collected.

**Table 4 T4:** Dummy table for abstinence from street heroin at final prescription as indicated by urine test

	Abstinence successful	Abstinence not successful	Totals
Buprenorphine	A	C	A+C
Dihydrocodeine	B	D	B+D
Totals	A+B	C+D	A+B+C+D

RR XX 95% CI XX-XX, NNT XX 95% CI XX-XX

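### Misuse of the trial drug is an outcome for both arms, but supervised consumption is named for buprenorphine only, so one between-arm ratio would mix misuse with the chance of its being seen (minor)

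*Protocol article*

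**What the plan says.** All references are to the protocol article.

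- **Outcome.** Inappropriate use of prescribed medication is a secondary outcome during detoxification. Its whole definition is one sentence: "Examples of this include intentional overdose and storing, trading, swapping or selling of prescribed medication". It states no source, rater or counting rule.
- **Supervision.** The Design section says "Some confounding variables cannot be randomised" and continues: "These include the inherent difference in the two detoxification programmes, i.e. the daily supervised consumption of buprenorphine".
- **Blinding.** "LEEDS is a pragmatic open label randomised controlled trial".
- **Data source.** For adverse events, "The LEEDS trial co-ordinator will extract data from clinical records, for the period of detoxification, and transcribe these to a database". The Data collection section describes taking background data from health records and adds: "There will be minimal additional contact with the participants". No separate check for misuse, applied to both arms, is described.
- **Tabulation.** The Analysis section says "Dummy tables have been constructed for all secondary outcomes" and that these were fixed in advance. The only example printed, Table 4, is a two-arm abstinence table with a relative risk and a number needed to treat.
- **Relevance.** The Background says "there has been a move away from prescribing dihydrocodeine due to its potential for diversion by prisoners into the prison shadow economy". The Discussion hopes that the results will influence prison prescribing policy.

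**The concern.** Supervised consumption can do two things to this outcome. It can prevent misuse, which is a real effect of the programme as delivered and belongs in the comparison. It also puts staff where they can see an attempt to hold back a dose, which changes what is recorded without changing what prisoners do. If supervision applies to one drug only, the recorded count in each arm is true misuse multiplied by an arm-specific chance of being noticed and written down.

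The Design section acknowledges the programme difference in general terms. It does not connect that difference to the one outcome that supervision most directly makes visible. Diversion is also the reason the Background gives for prescribers leaving dihydrocodeine, so readers are likely to look at this table for an answer about diversion.

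**Working it through.** **Inputs.** From the documents: 60 per arm and two-sided alpha 0.05 (Sample size); supervision named for buprenorphine (Design). Not in the documents: any misuse or detection rate. All such values below are assumptions.

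**The plan's own figures.** None is given for misuse. Table 1 gives power for 60 per arm. The pooled-variance normal approximation, power = Φ{[|p1 − p2|√n − 1.96√(2p̄(1 − p̄))] / √(p1(1 − p1) + p2(1 − p2))}, reproduces all 20 entries within 2 points (70% v 45%: 79.9%, stated 80%). Table 1 does not bear on this point, but the same formula is used in step 3.

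**Step 1: what the ratio measures.** With true misuse m and detection probability s in each arm (B = buprenorphine, D = dihydrocodeine):

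recorded RR = (m_B × s_B) / (m_D × s_D) = true RR × (s_B / s_D).

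The ratio is free of distortion only if s_B = s_D. Nothing in the article makes them equal.

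**Step 2: illustration with supervised detection s_B = 0.80.**

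| s_D | True 20% v 20% (true RR 1.00) | True 10% v 20% (true RR 0.50) |
|---|---|---|
| 0.72 | 0.160/0.144 = 1.11 | 0.080/0.144 = 0.56 |
| 0.60 | 0.160/0.120 = 1.33 | 0.080/0.120 = 0.67 |
| 0.40 | 0.160/0.080 = 2.00 | 0.080/0.080 = 1.00 |
| 0.30 | 0.160/0.060 = 2.67 | 0.080/0.060 = 1.33 |

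The first column only restates s_B/s_D. In the second, a true halving keeps its direction at 0.72 and 0.60, vanishes at 0.40 and reverses at 0.30.

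The detection ratio could also run the other way. If staff who know the allocation watch dihydrocodeine more closely, say s_B = 0.60 and s_D = 0.80, equal true misuse records 0.120/0.160 = 0.75.

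**Step 3: what this could do to a test.** With 60 per arm and 20% true misuse in both arms, the chance of a significant excess recorded on buprenorphine is:
- detection 90% v 30% (18% v 6% recorded): 53%
- detection 90% v 50% (18% v 10%): 24%
- detection 80% v 60% (16% v 12%): 9%

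The nominal rate in that one direction is 2.5%, half of the two-sided 5%. The approximation is rough, since 6% of 60 is only 3.6 expected events.

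**Step 4: attempted and completed misuse differ.** Assume that 20% attempt misuse in each arm, half of buprenorphine attempts are intercepted at supervised consumption and recorded, and 40% of the remaining misuse is detected in both arms.
- Intercepted: 20% × 0.5 = 10% on buprenorphine, none on dihydrocodeine.
- Completed: 20% − 10% = 10% v 20%, true RR 0.50.
- Recorded from sources open to both arms: 10% × 0.4 = 4% v 20% × 0.4 = 8%, RR 0.50.
- Recorded, all events: 10% + 4% = 14% v 8%, RR 1.75.

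Attempts are equal (RR 1.00). The all-events ratio of 1.75 matches neither attempts nor completed misuse. The common-source ratio matches completed misuse, but says nothing about attempts.

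**The case against.** The strongest reply is that much of this is inference. No sentence says that dihydrocodeine is unsupervised, and its administration is not described. The misuse table is not printed, so it may already code the source of each event, or may carry no relative risk. The article condenses a fuller protocol, and the coding of one secondary outcome is the kind of detail that such an article leaves out. The programme difference is openly declared, and in a pragmatic trial programmes are compared as delivered.

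Part of this stands. That dihydrocodeine is not supervised in the same way is a fair reading of the Design section, since supervision could hardly be the difference between programmes otherwise, but it remains a reading. It would be wrong to assert that the plan counts every record alike whatever its source. The pragmatic argument justifies counting prevention. It does not justify counting visibility as harm.

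A reader might go further and infer that the design makes dihydrocodeine look safer than it is, or that it will hide or reverse a true difference in diversion. The documents do not support that. Most of the listed acts (overdose, trading, swapping, selling) take place away from the dispensing point, and a buprenorphine tablet successfully concealed and then sold is as hidden as sold dihydrocodeine. In an open-label trial, the known concern about dihydrocodeine could raise its detection. Loss or reversal of a true halving appears in the illustration only at 40% or 30% detection against 80%, and those values are assumed.

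**Conclusion.** The point holds in a limited form. Given one-arm supervision (inferred from the Design section), apparent reliance on routine records, and tabulation by arm (implied by the Analysis section), a single between-arm ratio for misuse would combine true misuse with arm-dependent detection, and it would pool intercepted attempts with completed acts. The size and net direction cannot be derived from the documents; every relative risk above is an illustration under assumed rates. Any preventive effect of supervision is genuine and is not part of the bias.

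Severity is minor. The primary outcome rests on a urine test and is untouched by this problem. What is affected is the interpretation of one secondary harm outcome, though one that bears on the prescribing question the trial hopes to inform.

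**What to change.** - **Extraction.** For each misuse event, code where it was detected, as far as the record shows: at supervised consumption; from a source open to both arms; not stated.
- **Table.** In the pre-specified misuse table, give counts by arm twice: for all events, and for completed misuse from sources open to both arms.
- **Intercepted attempts.** List attempts stopped at supervised consumption descriptively by arm.
- **Statement.** Say in the table note that the all-events relative risk is not to be read as a difference in diversion between the drugs.

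Because the tables are fixed in advance, this should be settled before outcome data are seen.

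The cost is one extra extraction field and one revised table. The common-source comparison will have fewer events and less precision, and it measures completed and not attempted misuse. Some records will not state a source. No change to the supervision of either drug is proposed.

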###### Service related outcomes

Admission to hospital, Accident and Emergency and in patient stays in prison healthcare will be recorded.

##### At one-month, three-month and six-month post detoxification

###### Abstinence status

Evidence of this taken from clinical notes if the participant is still in HMP Leeds or has been transferred to another prison. If the participant has been released into the community then they will be contacted via address or telephone number given at point of randomisation, or by accessing local community drugs service records.

###### Service utilisation

Contacts with hospitals and Accident and Emergency departments will be noted. For those participants still in the prison estate, use of inpatient prison healthcare will be recorded.

The project team recognise the difficulty in tracking people with drug problems who have subsequently been released from prison across this period.

#### Data collection

The outside of the allocation envelope will be completed by the prison doctor before opening. This will record Unit number, date of birth and estimate of severity of addiction and expected prognosis.

The LEEDS trial co-ordinator will collect details of drug of allocation, background history, and use of opiates from the participant's health records. The primary outcome and data at one, three months and six months after randomisation will again be collected by the LEEDS trial co-ordinator. There will be minimal additional contact with the participants. LEEDS is designed to avoid the complication of the care provided to this group.

All data will be double entered into an EPI-INFO database customised for the LEEDS project and the simple analysis involved with this project will also be undertaken in that package.

#### Analysis

After data entry, all analysis will be undertaken in Epi-info. The analysis of the primary outcomes will be of a simple 2 × 2 table (see Table 4, below). Dummy tables have been constructed for all secondary outcomes. These tables are designed to be rigid templates for the final write up of the project, and to protect the researchers from bias, once the data are disclosed. An example is given below, but dummy tables for all data to be collected have been constructed, *a priori*, for every variable to be collected.

**Table 4 T4:** Dummy table for abstinence from street heroin at final prescription as indicated by urine test

	Abstinence successful	Abstinence not successful	Totals
Buprenorphine	A	C	A+C
Dihydrocodeine	B	D	B+D
Totals	A+B	C+D	A+B+C+D

RR XX 95% CI XX-XX, NNT XX 95% CI XX-XX

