### Sample size

Currently no randomised controlled trials relevant to these comparisons have been undertaken in the prison setting. However, from the results of our community study comparing these agents we estimate that with a sample size of 120 we will have a finding of clinical and statistical significance. Power calculations were undertaken using Sample Power 1.20 developed by SPSS Inc., comparing two groups (60 individuals in each) and for α = 0.05 (two-sided). The power calculations are shown below in Table 1.

**Table 1 T1:** Power calculations for sample of 120Difference between groups

	**Power**	**Difference between groups**	**Power**
70% × 60%	21%	40% × 30%	21%
70% × 50%	61%	40% × 20%	67%
70% × 45%	80%	40% × 15%	88%
70% × 40%	92%		
60% × 50%	20%	30% × 20%	24%
60% × 40%	59%	30% × 15%	50%
60% × 35%	79%	30% × 10%	79%
60% × 30%	92%		
50% × 40%	20%	20% × 15%	11%
50% × 30%	61%	20% × 10%	33%
50% × 25%	82%	20% × 5%	70%

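### The primary analysis is a valid but unadjusted 2 × 2 table with no stated role for the severity and prognosis ratings recorded before allocation: a possible loss of efficiency of unknown size

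*Protocol article*

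**What the plan says.** All references are to the protocol article.

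- **Analysis:** "The analysis of the primary outcomes will be of a simple 2 × 2 table". The dummy table ends with "RR XX 95% CI XX-XX, NNT XX 95% CI XX-XX" and includes no covariate or stratum. Of the dummy tables in general it says "These tables are designed to be rigid templates for the final write up of the project". It adds that such tables were built in advance for every variable to be collected, but prints only one.
- **Data collection:** "The outside of the allocation envelope will be completed by the prison doctor before opening". Of the entry itself: "This will record Unit number, date of birth and estimate of severity of addiction and expected prognosis".
- **Design:** randomisation uses blocks of random size and consecutively numbered envelopes. No stratification factor is stated.
- **Sample size:** 60 per group, "α = 0.05 (two-sided"). Table 1 gives power for a range of pairs of proportions and names no single target difference.

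**The concern.** Both ratings are fixed before the allocation is known, so allocation cannot influence them, and they are planned for every participant. A baseline variable of that kind can be adjusted for without endangering the randomised comparison. If it predicts outcome, adjustment removes noise.

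Precision matters here because Table 1 gives only 59–67% power for 20-point differences from 40% upwards and 79–82% for 25-point differences from 50% upwards. The Discussion expects a significant result to influence prison healthcare policy.

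Timing matters too. The article fixes its tables in advance to guard against bias once data are seen, so an adjusted analysis added after disclosure would be a departure from the plan.

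**Working it through.** **1. Reproduce Table 1.** Inputs: n = 60 per group and two-sided α = 0.05 (Sample size). The formula is the normal approximation with pooled variance under the null:

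power = Φ{ [ |p1−p2| − 1.96·√(2p̄(1−p̄)/n) ] / √([p1(1−p1)+p2(1−p2)]/n) }

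- 50% v 30%: (0.20 − 1.96·√(2·0.40·0.60/60)) / √((0.25+0.21)/60) = (0.200 − 0.1753)/0.0876 = 0.282, so power is 61.1%. Table 1 has 61%.
- 60% v 35%: (0.25 − 1.96·√(2·0.475·0.525/60)) / √((0.24+0.2275)/60) = (0.250 − 0.1787)/0.0883 = 0.808, so power is 79.0%. Table 1 has 79%.

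All 20 entries reproduce within 2 points. Table 1 is therefore correct for the crude comparison that the article plans.

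**2. What adjustment could gain.** The article gives neither the scale of the ratings nor their prognostic strength. Assumption: the prognosis rating forms two equal groups whose abstinence differs by g points in both arms. The share of outcome variance explained is R² = (g²/4)/v, where v is the mean of p(1−p) over the arms. The effective size per arm is 60/(1−R²), which goes into the formula in step 1.

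For 60% v 35%, v = (0.24+0.2275)/2 = 0.23375. For 50% v 30%, v = (0.25+0.21)/2 = 0.23.

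| Assumed gap g | R², 60 v 35 | Effective n | Power | R², 50 v 30 | Effective n | Power |
|---|---|---|---|---|---|---|
| 0 | 0 | 60 | 79.0% | 0 | 60 | 61.1% |
| 20 points | 0.043 | 62.7 | 80.8% | 0.043 | 62.7 | 63.1% |
| 30 points | 0.096 | 66.4 | 83.0% | 0.098 | 66.5 | 65.6% |
| 40 points | 0.171 | 72.4 | 86.1% | 0.174 | 72.6 | 69.5% |
| 50 points | 0.267 | 81.9 | 90.1% | 0.272 | 82.4 | 75.0% |

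**3. Simulation check.** 40,000 trials per scenario, comparing the crude uncorrected chi-squared test with the Cochran-Mantel-Haenszel test:

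| Assumed gap | 60 v 35: crude → stratified | 50 v 30: crude → stratified | Change in variance of risk difference |
|---|---|---|---|
| 0 | 80.4 → 79.5% | 61.7 → 61.0% | about +1% |
| 20 points | 80 → 81% | 62 → 63% | about −4% |
| 30 points | 80 → 83% | 62 → 66% | about −9% |
| 40 points | 80 → 86% | 62 → 70% | about −17% |
| 50 points | 80 → 90% | 62 → 75% | about −26% |

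At 50% v 50% the stratified test rejects in about 5% of trials and the crude test in 5.3–5.6%.

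**4. A different model.** With one continuous prognostic score and a covariate-adjusted logistic test (4,000 runs per scenario), 70% v 50% gives these adjusted v crude powers:

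- odds ratio per SD 1.0: 60.0 v 60.4%
- odds ratio per SD 1.5: 64.2 v 61.7%
- odds ratio per SD 2.0: 66.5 v 61.8%
- odds ratio per SD 3.0: 69.5 v 60.7%

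The gain is again between nil and about 9 points.

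**5. Would adjustment rescue a 20-point difference?** 80% power for 70% v 50% needs 93 per group, so 60 per group would need R² = 1 − 60/93 = 0.355. In the model of step 2 that means g = 2·√(0.355·0.23) = 0.57, a 57-point gap in abstinence between rating groups. That lies beyond the whole range tried above.

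**The case against.** The strongest reply is that nothing here is wrong. An unadjusted comparison of two proportions is valid under randomisation. It matches the power calculation, ignores no stated stratification factor, and keeps analytic choices to a minimum on purpose. All of that stands.

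Four stronger readings are tempting, and the article does not support them.

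- **The ratings are never used.** The article says dummy tables exist for every variable collected and prints only one. The ratings may appear in tables that are not shown. What can be said is that no role in the primary comparison is stated.
- **Free precision is thrown away.** The ratings are a doctor's estimates made at reception into prison, with no scale, categories or validation given. A 50-point gap around the 47.5% average of 60% and 35% means roughly 72% v 22% abstinence separated by one subjective rating. At a 20-point gap the gain is only 1 to 2 points. The gain could be nil, and adjustment is not costless.
- **Chance imbalance biases the result.** With 60 per arm and a 50/50 rating, the arms differ by 10 points or more on the rating in about three trials in ten. Under a 40-point gap, a 10-point imbalance moves the crude risk difference by 0.10 × 0.40 = 4 points. The crude interval and test already allow for this over repeated randomisations, so it is noise and not bias.
- **Adjustment would cure the marginal power.** Step 5 of the working shows otherwise.

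What survives the reply is the narrower point. The article does fix the primary method, in templates it calls rigid, and suitable pre-allocation data are already to be collected. The choice therefore has to be made before data are disclosed.

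**Conclusion.** The point holds as a possible loss of efficiency. It is not an error, a bias or a contradiction.

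If the prognosis rating splits participants evenly and abstinence differs by 0 to 50 points between the groups, stratification changes power by about −1 to +10 points for 60% v 35% and about −1 to +13 points for 50% v 30%. The variance of the risk difference changes by between about +1% and −26%, and type I error stays near 5%. The split and the gaps are assumptions, because the article gives no figure for prognostic strength. The lower end of the range is as compatible with the document as the upper end.

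The case for changing rests on asymmetry: less than 1 point of power is lost if the rating is uninformative, and several points may be gained if it is informative.

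**What to change.** Before data are disclosed, state one primary analysis: a Mantel-Haenszel relative risk and risk difference, each with a 95% CI, stratified by the prognosis rating written on the envelope before opening. Derive the NNT from the stratified risk difference, so that the measures promised under Table 4 are still reported. Fix the rating's categories or cut-point now, along with a category for missing ratings. Keep crude Table 4 as the supportive result.

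The cost is a sentence or two in the Analysis section, one more dummy table, and a check that the named analysis package produces the stratified estimates and intervals. No new data are needed. The downsides are that a cut-point must be chosen for a rating whose scale the article does not describe, and that under 1 point of power is lost if the rating predicts nothing.

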**Methods/Design:**

The Leeds Evaluation of Efficacy of Detoxification Study (LEEDS) Prisons Pilot Study will use randomised controlled trial methodology to compare the open use of buprenorphine and dihydrocodeine for opiate detoxification, given in the context of routine care, within HMP Leeds. Prisoners who are eligible and give informed consent will be entered into the trial. The primary outcome measure will be abstinence status at five days post detoxification, as determined by a urine test. Secondary outcomes during the detoxification and then at one, three and six months post detoxification will be recorded.

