### Interventions

The treatment option will be concealed from both participant and clinician at time of assessment. Both parties will remain blind to the selected treatment option until the envelope is opened.

1. Dihydrocodeine, given openly, in the context of the standard prison doctor and drugs worker support.

2. Buprenorphine, given openly, in the context of the standard prison doctor and drugs worker support.

The reducing regimen of both dihydrocodeine and buprenorphine (over less than 16 days) will be at the discretion of the prescribing doctor. However, the dose should not exceed this standard regime (Table 2 and Table 3).

**Table 2 T2:** Buprenorphine detoxification

**Day**	**Dose (mg)**
1	6
2	8
3	8
4	6
5	6
6	4
7	3.6
8	3.2
9	2.8
10	2.4
11	2.0
12	1.6
13	1.2
14	0.8
15	0.4

**Table 3 T3:** Dihydrocodeine detoxification

Day	Morning	Evening
1	XXXX	2 × 120 mg
2	2 × 120 mg	2 × 120 mg
3	1 × 120 mg 1 × 90 mg	1 × 120 mg 1 × 90 mg
4	1 × 120 mg 1 × 90 mg	1 × 120 mg 1 × 90 mg
5	2 × 90 mg	2 × 90 mg
6	2 × 90 mg	2 × 90 mg
7	1 × 90 mg 1 × 60 mg	1 × 90 mg 1 × 60 mg
8	1 × 90 mg 1 × 60 mg	1 × 90 mg 1 × 60 mg
9	2 × 60 mg	2 × 60 mg
10	2 × 60 mg	2 × 60 mg
11	1 × 60 mg	2 × 60 mg
12	1 × 60 mg	2 × 60 mg
13	1 × 60 mg	1 × 60 mg
14	1 × 60 mg	1 × 60 mg
15	XXXX	1 × 60 mg

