### Outcomes

#### Primary outcome

Abstinence from street opiates at five days post detox as indicated by urine test. Should the person not finish the course of detoxification or refuse to give urine then this will be considered as a positive urine test for opiates.

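### The table assigned to the primary analysis is captioned for a different time point (final prescription) from the defined primary outcome (five days post detox)

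*Protocol article*

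**What the plan says.** The protocol article describes the primary outcome in three places.

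- **Abstract, Methods/Design:** "The primary outcome measure will be abstinence status at five days post detoxification, as determined by a urine test".
- **Outcomes, Primary outcome:** "Abstinence from street opiates at five days post detox as indicated by urine test". A rule for incomplete data follows: "Should the person not finish the course of detoxification or refuse to give urine then this will be considered as a positive urine test".
- **Analysis:** "The analysis of the primary outcomes will be of a simple 2 × 2 table (see Table 4, below". The caption of Table 4 is "Dummy table for abstinence from street heroin at final prescription as indicated by urine test", and the table ends with placeholders for a relative risk and an NNT, each with a 95% CI.

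Two sentences in the Analysis section bear on the status of Table 4. One describes the dummy tables: "These tables are designed to be rigid templates for the final write up of the project". The article adds that they are there to guard against bias once the data are known. The other introduces the table itself: "An example is given below, but dummy tables for all data to be collected have been constructed".

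**The concern.** The Analysis section sends the reader to Table 4 for the primary analysis, but the caption does not describe the primary outcome defined elsewhere. It differs in time point and in the substance named.

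At stake is which endpoint the trial's headline relative risk and NNT belong to. Abstinence at the last prescription and abstinence five days after detoxification ends are different clinical states: the first is measured at or near the end of treatment, the second after a gap without it. The trial is open label, so the primary outcome should have a single definition before any data are disclosed. The dummy tables are meant to secure exactly that, and a template with the wrong caption works against its own purpose.

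**Working it through.** This is a comparison of text; the arithmetic only supports it.

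**1. The definitions side by side**

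| Feature | Abstract | Primary outcome section | Table 4 caption |
|---|---|---|---|
| Time point | five days post detoxification | five days post detox | final prescription |
| Substance | not named | street opiates | street heroin |
| Measurement | urine test | urine test | urine test |
| Non-completion or refused urine | not stated | counted as positive | not stated |

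The Abstract and the Primary outcome section agree on timing, and the caption disagrees with both. The heroin/opiates difference is weaker evidence. Both versions rest on a urine test, and the Background uses heroin as its leading example of an illicit opiate.

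**2. Could Table 4 belong to another listed outcome?** The secondary outcomes during detoxification are adverse events, leaving the study early, inappropriate use of medication and service-related outcomes. None is an abstinence measure. The later secondary abstinence outcomes are at one, three and six months. No listed outcome is abstinence at final prescription, so the caption cannot be read as the template for something else.

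**3. How far apart are the time points?** The Interventions section states: "The reducing regimen of both dihydrocodeine and buprenorphine (over less than 16 days) will be at the discretion of the prescribing doctor". Tables 2 and 3 end on day 15. On the full standard schedule, and assuming that post detox is counted from the last dose:

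- Table 4 caption: about day 15
- Primary outcome section: 15 + 5 = about day 20

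A shorter regimen moves both days earlier. Final prescription is not defined, and for someone who leaves early it could fall on any day. The non-completion rule settles such cases for the five-day outcome, but nothing attaches that rule to a final-prescription outcome.

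**4. Is the sample size affected?** Table 1 gives power for 60 per arm at two-sided α = 0.05. Its figures can be reproduced with the pooled normal approximation:

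power = Φ{ [ |p1 − p2|·√n − 1.96·√(2·p̄·(1 − p̄)) ] / √(p1(1 − p1) + p2(1 − p2)) }

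For 70% v 45%, p̄ = 0.575:

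- |p1 − p2|·√n = 0.25 × 7.746 = 1.936
- 1.96 × √(2 × 0.575 × 0.425) = 1.96 × 0.699 = 1.370
- √(0.21 + 0.2475) = 0.676
- (1.936 − 1.370) / 0.676 = 0.837, and Φ(0.837) = 79.9%, against 80% stated

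All 20 cells reproduce within 2 points. No pair of rates is tied to a time point or a substance, so correcting the caption changes nothing in Table 1. For the same reason, no power for one definition against the other can be calculated.

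**The case against.** The strongest reply is that this is a caption slip. Two explicit and agreeing definitions outweigh one caption, and the section headed Primary outcome gives the full definition with its rule for incomplete data. The sentence on rigid templates directly follows one about dummy tables for the secondary outcomes, so its nearest reading concerns those tables. Table 4 is also introduced as an example. All of this stands, and it weakens any claim that the caption binds the analysis. It does not remove the conflict, because the same paragraph names Table 4 as the place for the primary analysis.

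A reader might infer three stronger things that the documents do not support.

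- **That the trial would analyse the wrong endpoint.** This holds only if the caption is followed literally.
- **That the team could choose between two sets of results after seeing them.** The article schedules no urine test at final prescription; the only urine test tied to an outcome time point is the five-day one. This also points to a labelling error rather than a live competing primary.
- **That a test at final prescription would be biased against one arm because a trial drug shows on the assay.** The article does not describe the assay or say that either drug reads positive on it, so no size can be given for such a bias.

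**Conclusion.** The concern holds as an internal contradiction in the specification of the primary analysis. The time point is the substantive conflict; heroin versus opiates is secondary. The caption matches no outcome the protocol lists, so a report that followed the template as printed would attach its headline relative risk and NNT to an undefined endpoint.

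The separation of about 5 days (day 15 versus day 20) assumes the full standard schedule and counting from the last dose. The article gives no abstinence rate by time point or substance, so the effect on the estimated difference cannot be sized, and none is claimed. Sample size and power are untouched. The point should be corrected before data are disclosed because it concerns the primary outcome of an open-label trial and costs almost nothing to settle.

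**What to change.** Retitle Table 4 with the definition from the Primary outcome section, "Abstinence from street opiates at five days post detox as indicated by urine test", and add to the caption that non-completion of detoxification or refusal of urine is counted as positive. That rule decides who enters the cells for unsuccessful abstinence, so it belongs with the table. State in the Analysis section that this is the only primary-outcome table. If a final-prescription urine result is wanted, list it as a secondary outcome with its own table.

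The cost is one caption and one sentence. The correction needs no new data and no additional participants.
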